
Baseline demographic variables collected by means of parental interviews* or from medical records +.

The feeding intervention continued for 90 days including transfer to a participating level II unit or until discharge home, whichever occurred first. Other than whether infants received donor milk or preterm formula as a supplement, all other aspects of feeding were directed by the clinical team at each NICU. General feeding guidelines were agreed upon by the participating NICUs to provide a consistent approach, and to set criteria necessitating removal from the feeding protocol. These detailed guidelines are found in Table 
4. Donor milk was purchased and shipped primarily from the Mother’s Milk Bank of Ohio (>95%) with backup from Calgary Mother’s Milk Bank, both HMBANA members. Donor milk from Ohio was collected and pooled from at least three women who had delivered within the previous three months. Once nutrient fortification of donor milk commenced, a protein module (0.3 g/dl, Beneprotein, Nestle) was added to donor milk to bring the analyzed protein content (0.9 g/dl) up to the average estimated protein concentration of mother’s own milk after 30 days (1.2 g/dl)
[71,72].

**Table 4 T4:** Feeding guidelines

	**Supplement to MOM**	**Supplement to MOM**
	Pasteurized Human Donor Milk	Preterm Formula*
		Similac Special Care 20 or 24 kcal/ oz [3.0 g protein/100 kcal] [Abbott Laboratories] or
		Enfamil Premature Formula 20 or 24 kcal/oz [3.0 g protein/100 kcal] [Mead Johnson Nutritionals]
**Initiation of enteral feeding**	Day 1-7	Day 1-7
**Volume of feeding at initiation**	10-20 ml/kg/d (hold volume for 3-5 days)	10-20 ml/kg/d (hold volume for 3–5 days)
**Rate of feed advancement**	10-25 ml/kg/day	10-25 ml/kg/day
**Fortification to commence at >120 ml/kg/day using milk pumped > 7 days after parturition+**	Human milk fortifier	Not Applicable
	Enfamil Human Milk Fortifier, [Mead Johnson Nutritionals] or	
	Similac Human Milk Fortifier, [Abbott Laboratories]	
**Volume**	140-200 ml/kg/d to achieve a weight gain of > 15 g/kg/day	140-200 ml/kg/d to achieve a weight gain of > 15 g/kg/day
**Minimum protein dose to be provided once (or up to 3 days after) volume reaches >150 ml/kg/d**	3.0 g/kg/d**	3.0 g/kg/d**
**At 24 kcal/oz and weight gain < 15 g/kg/d for 3–7 days**	Concentrate feeding using a multi-nutrient modular to 26–27 kcal/oz	Modular to 26–27 kcal/oz

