### Inclusion/exclusion criteria

The inclusion criteria were (1) day 1 to 4 of life; (2) <1500 g birth weight; (3) enteral feeding expected to be initiated in the first 7 days of life. The exclusion criteria were (1) infants with serious congenital or chromosomal anomalies that may contribute to poor developmental outcome; (2) severe asphyxia; (3) enrolment in any other clinical study affecting nutritional management during the feeding intervention; (4) reasonable potential that the infant would be transferred to a NICU where the study protocol could not be continued. The study feeding protocol was stopped if (1) the infant died during the intervention period; (2) a parent(s) requested withdrawal from the feeding protocol; (3) the infant had inadequate weight gain despite nutrient concentration of feedings (4) there was a requirement for thickening of feeds that would unmask the feeding assignment. In the event that an infant was withdrawn from the study feeding protocol, the family was requested to allow Research Staff to continue data collection and to complete the follow-up phase after discharge. See Figure 
2 for a review of subject disposition to date.

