### Outcome measures

The primary outcome for this trial is the cognitive composite score on the BSID-III at 18 months CA. The BSID-III is a standardized test designed to assess the cognitive, language and motor (fine, gross) development of infants from 1 to 42 months of age
[73]. A decision was made to administer this test at each infant’s 18 month CA birth date because of the improved predictive validity at this time compared to earlier ages
[73,74].

The secondary mortality/morbidity composite comprised death and major morbidity including NEC, late onset sepsis, chronic lung disease or severe retinopathy of prematurity. Late onset sepsis was defined as a positive culture from blood, cerebrospinal fluid, catheter or suprapubic urine at >5 days after birth. A confirmed case of NEC was defined as stage 2 or 3 by the Modified Bell Staging Criteria
[75]. Infants were classified as having chronic lung disease as assessed at 36 weeks postconception by NIH criteria
[76]. Severe ROP (Stage 4 or 5) was defined according to International criteria or if laser surgery or intraocular anti-vascular injection was required
[77-79].

Weight (+/-2 g), length (+/-0.1 cm) and head circumference (+0.1 cm) were measured weekly during hospitalization and at routine post-discharge clinic visits using standardized procedures and precision equipment as previously described
[80,81]. To account for the different GA of infants, z-scores for anthropometric measurements are computed using the Fenton preterm growth charts and the World Health Organization Growth Standard after 50 weeks gestational age
[82]. Changes in weight as a consequence of the intervention will be specifically examined in relation to gains in length and head circumference as there is little evidence that weight gain alone (i.e. fat mass gain) will benefit the long-term outcome of infants.

Exploratory variables include feeding tolerance and nutrient intakes during the feeding intervention. The volume and estimated energy/nutrient density of study milk and other sources of nutrition (e.g. parenteral nutrition, mother’s own milk, vitamin supplements) were extracted prospectively from medical records by study staff during the feeding intervention. Feeding tolerance will be assessed by describing the days to full enteral feeding (150 ml/kg/d) and number of days feedings were withheld.

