### Statistical analyses

Using a 5 point difference in composite cognitive scores at 18 months CA, with 80% power (alpha level of 0.05), and an estimated standard deviation in each feeding group of 15, we estimated that we required 142 infants in each feeding arm. We assumed a 10% loss to follow-up during the feeding intervention and an additional 10% loss to follow-up after discharge, thus necessitating 176 infants to be randomized in each of the two feeding groups. As the number of infants withdrawn from the study exceeded 10%, primarily due to infant death, we overenrolled by 11 subjects to produce a final sample size of 363 subjects.

Analyses will be carried out using SAS Version 9.1 (SAS Institute, Cary, NC, USA). Descriptive statistics will be calculated for all variables of interest. Continuous measures will be summarized using means and standard deviations whereas categorical measures will be summarized using counts and percentages. The primary analysis for this intent-to-treat study will include all infants as randomized, regardless of adherence with the feeding protocol. The initial analysis will be a comparison of means (cognitive composite score) between the 2 groups at 18 months CA. A generalized linear model will carry out this comparison, controlling for length of treatment and adjusting for correlation of observations taken at the same centre. Sex, birth weight strata (<1000, 1000–1499 g), use of antenatal steroids, multiple birth, a count of key morbidities and duration of mother’s own milk-feeding are prognostic of neurodevelopmental outcome, and for this reason we will perform a secondary analysis which will include a regression model adjusted for the aforementioned characteristics
[4,6,13].

Children who cannot be tested on the BSID-III due to disability, severe delay or who perform below the threshold of the test for individual composite scores (cognitive, language motor) will be assigned a score of 49
[7]. The scores will be computed by trained individuals who have established inter rater reliability (R^2^ = 80) and who are blind to study group. Other missing data will be handled using methods of multiple imputation.

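### The primary intention-to-treat model adjusts for length of treatment, a post-randomisation variable the feeds can change, so it does not estimate the effect of assignment

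*Protocol article*

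**What the plan says.** The outcome is clear: "The primary outcome for this trial is the cognitive composite score on the BSID-III at 18 months CA". So is the analysis principle, in Statistical analyses: "The primary analysis for this intent-to-treat study will include all infants as randomized, regardless of adherence with the feeding protocol". The same paragraph then describes a comparison of mean cognitive scores between the two groups, and says a generalized linear model will make that comparison, "controlling for length of treatment and adjusting for correlation of observations taken at the same centre". Other prognostic factors (sex, birth-weight stratum, antenatal steroids and so on) are kept for a separate secondary regression. The article describes no primary model without length of treatment.

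Two other places show what this variable is. Methods/Design says: "The feeding intervention continued for 90 days including transfer to a participating level II unit or until discharge home, whichever occurred first". The Inclusion/exclusion criteria section lists the reasons for stopping the feeding protocol early: death, parental request, a need for thickened feeds, and that "the infant had inadequate weight gain despite nutrient concentration of feedings". Table 4 also removes infants from the feeding protocol when weight gain stays low at the highest feed concentration.

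**The concern.** The planned period is the same in both arms, so differences between infants in treatment length arise only from events after randomisation. The protocol gives reasons why the assigned milk could change those events:

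- Study objectives hypothesises that donor milk reduces death and serious morbidity, including NEC and late-onset sepsis. Less of these would tend to shorten stay.
- The section on pasteurized donor human milk cites a relative risk of NEC of 2.5 on formula. It also cites slower weight, length and head growth on donor milk, which could lengthen stay or cause more removals.
- Outcome measures, in the health-economic text, anticipates different therapeutic needs by arm if growth or NEC differ.

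The Background names the same morbidities and poor growth as determinants of neurodevelopment. Length of treatment may therefore be affected by arm and also share causes with the outcome. Conditioning on it can remove any part of the effect that runs through clinical course. It also opens a non-causal path through illness severity, which drives both stay and cognition. The sole primary result would then depend on the feeds leaving treatment length unchanged, although Study objectives asks about the total effect of a feeding policy.

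**Working it through.** **Inputs from the protocol (Statistical analyses).** Target difference: 5 points. SD: 15 per arm. Power: 80%. Alpha: 0.05. The plan arrives at 142 infants per arm, or 176 after two successive 10% losses. Final enrolment was 363.

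**Reproducing the plan's figures.** n = 2 × (1.960 + 0.842)² × 15² / 5² = 141.3, so 142 per arm (two-sided). 142 / (0.9 × 0.9) = 175.3, so 176. 2 × 176 + 11 = 363. Power at 142 per arm is 80.2%. All figures agree, and they describe an unadjusted comparison of two means.

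**What the adjusted model estimates.** Let τ be the total effect of assignment, a the arm difference in mean treatment length (days, donor minus formula), and b the within-arm slope of score on length (points per day). In a linear model the arm coefficient adjusted for length is

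adjusted coefficient = τ − b × a.

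This equals τ only if a = 0 or b = 0. The documents give neither quantity, so both are **assumed** below: a of 3 to 10 days either way, b of -0.1 to -0.3 points per day (longer stay marking sicker infants), and a within-arm SD of length of 25 days.

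**Worked example.** With a = -5 and b = -0.2, the coefficient is 5 − (-0.2)(-5) = 4.0. The correlation is r = -0.2 × 25 / 15 = -0.33, the residual SD is 15 × √(1 − 0.33²) = 14.1, and the SE is 14.1 × √(2/142) = 1.68. Power is Φ(4.0/1.68 − 1.96), about 66%.

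**Grid, true effect 5 points, 142 per arm** (power ignores the small extra variance from the arm-length correlation):

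| a (days) | b = -0.1 | b = -0.2 | b = -0.3 |
|---|---|---|---|
| 0 | 5.0 (81%) | 5.0 (85%) | 5.0 (90%) |
| -3 | 4.7 (76%) | 4.4 (75%) | 4.1 (76%) |
| -5 | 4.5 (73%) | 4.0 (66%) | 3.5 (62%) |
| -10 | 4.0 (63%) | 3.0 (43%) | 2.0 (25%) |
| +3 | 5.3 | 5.6 | 5.9 |
| +5 | 5.5 | 6.0 | 6.5 |
| +10 | 6.0 | 7.0 | 8.0 |

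**No true effect.** The bias is |a × b|, from 0.3 to 3.0 points. The two-sided rejection rate runs from 5.3% (3 days, 0.1) through 9.2% (5 days, 0.2) to 49% (10 days, 0.3), against a nominal 5%.

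**Simulation with the 90-day cap.** The score has SD 15. A latent severity is worth 6 points per SD and correlates 0.6 with uncapped stay (SD 22 days). Treatment length is restricted to 7 to 90 days and has no causal effect on the score. All these values are assumed.

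| Mean uncapped stay | Net difference in treatment | 5 points becomes | Power | Null bias | Null rejection |
|---|---|---|---|---|---|
| 75 days | about -4 days | about 4.2 | about 68% | about -0.75 | about 7% |
| 75 days | about -8 days | about 3.5 | about 50% | about -1.5 | about 14% |
| 90 days | about -2.7 days | about 4.4 | about 71% | about -0.6 | about 6.5% |
| 90 days | about -5.9 days | about 3.7 | about 55% | about -1.3 | about 11.5% |

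The 90-day rows matter because the Discussion gives 90 days as the average stay at the recruiting units. About half the infants then reach the cap, which compresses the arm difference. Without the covariate, the same data return 5 points, or zero under the null.

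**The case against.** The best defence is that no bias has been shown. The arm coefficient is distorted only if the arms differ in treatment length, and the documents report no such difference. The two mechanisms pull in opposite directions and may partly cancel. Clinical teams are blinded, Table 4 steers both arms to the same weight-gain target, donor milk receives added protein, and much of the slower-growth evidence predates current fortification. If the arms do not differ in length, the covariate even helps: the a = 0 row shows power of 81% to 90%.

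All of this stands as a limit on size. With the protocol's own average stay of 90 days the bias is smaller than with 75, and the largest losses of power occur only at the largest assumed shifts. The sign of the slope is also uncertain, because an infant removed early for poor growth has a short treatment and may be sicker. Death has a direct bearing only if scores are imputed for infants who die, which the article does not say. The simulation represents only the shared-severity path and not mediation, although the formula covers both. The intention-to-treat population is correctly defined; the fault is the covariate.

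None of it rescues the choice. A primary analysis should not be valid only if the intervention leaves clinical course unchanged when the secondary hypotheses say it will change it. The precision argument can be met with baseline variables: gestational age and birth weight are already collected (Table 3).

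**Conclusion.** The point holds. As written, the primary model conditions on a post-randomisation variable that the assigned feed can affect, so its arm coefficient is not protected as the intention-to-treat effect that the objectives call for. Direction and size cannot be fixed from the documents. Under the assumed grid a true 5-point effect could be reported as anything from 2.0 to 8.0 points. In the capped simulation with a 90-day mean stay and donor milk shortening treatment, it becomes about 4.4 or 3.7 points. The bias is zero only if the arms have the same treatment length or length is unrelated to score within arms. The sample-size calculation is unaffected. This must be corrected because it alters what the sole primary result means, whatever the bias proves to be.

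**What to change.** Remove length of treatment from the primary model. State that the 18-month cognitive composite will be compared using randomised arm plus baseline terms only: centre and birth-weight stratum (the stratification factors), with gestational age at birth added if more precision is wanted. Report length of treatment by arm as a descriptive outcome, with reasons for early stopping. Label any model that includes it as exploratory.

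The cost is one sentence in the protocol or SAP, made before unblinding. The article says follow-up is still underway and outcome assessors are blinded. No new data or patients are needed, and 142 per arm still gives 80% power because that figure was derived without the covariate.

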## Methods/Design

This is a pragmatic multi-centre, double-blind, RCT designed to evaluate the effectiveness of pasteurized donor milk as a supplement to mother’s own milk in those infants when mother’s own milk is unavailable. The analysis will be conducted using an “intention to treat” approach. Infants randomized to the intervention group received donor milk when mother’s own milk was unavailable. Infants randomized to the control group received formula designed for preterm infants when mother’s own milk was unavailable.

Funding was received from the Canadian Institutes for Health Research (MOP#210093), SickKids Foundation and the Ministry of Health and Longterm Care of Ontario. Infants were recruited in one of four participating level III NICU in Toronto and Hamilton, Canada. A comprehensive list of parental and infant demographic variables was collected after written informed consent was secured (Table 
3). Randomization, performed within 96 hours of birth, was done centrally using a 24 hr/day web-based third party randomization service (Centre for Mother Infant and Child Research, Toronto). The study allocation was randomly assigned in a ratio of 1:1, in random blocks of 4 and 8, with stratification by centre and birth weight grouping (<1000 g and 1000–1499 g). Aside from the research dietary technicians assigned to the study and a single neonatal dietitian, all members of the research study team (including outcome assessors), clinical teams and families are blinded to study allocation.

**Table 3 T3:** Demographic variables collected during the DoMINO trial

**Infant characteristics**	**Prenatal and parental characteristics**
Gestational age at birth+	Gravity/Parity*
Birth weight, length and head circumference+	Artificial reproductive technology (type and origin of eggs, sperm)+
Size for gestational age (small [SGA], appropriate [AGA] or large for [LGA] gestational age)+	Antibiotic use prior to delivery (prior 2 weeks)+
Sex+	Use of Prenatal Steroids+
Multiple birth status+	Cesarean delivery*
5-minute Apgar score+	Mom has previously breastfed (yes/no)*
Newborn Illness severity score (SNAP-II+)	Mom intends to breastfeed (yes/no)*
	Parental education (highest degree or diploma attained)*
	Parental weight and height (self-reported)*
	Parental age*
	Number of children in current household*
	Smoking (maternal history during pregnancy)*
	First language spoken in the home*
	Socioeconomic status (single parenting; above or below poverty line)*
	Ethnicity*

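### The primary model allows for correlation within centre but not between siblings, so its standard error can be off in a direction that depends on an unstated sibling allocation

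*Protocol article*

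**What the plan says.** All references are to the protocol article.

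- **Primary model (Statistical analyses).** A generalized linear model compares mean cognitive composite scores, controls for treatment duration, and does so "adjusting for correlation of observations taken at the same centre". Centre is the only source of correlation named.
- **Secondary model (Statistical analyses).** The adjusted regression lists, among other prognostic factors, "use of antenatal steroids, multiple birth, a count of key morbidities". This is the only place in the analysis where multiple birth appears.
- **Eligibility (Inclusion/exclusion criteria).** Nothing excludes twins or triplets, and Table 3 records "Multiple birth status" at baseline.
- **Randomization (Abstract; Methods/Design).** Infants are described as the randomized unit, 1:1, in blocks of 4 and 8, stratified by centre and birth-weight group, at four centres. No rule for siblings is given.
- **Sample size (Statistical analyses).** "we estimated that we required 142 infants in each feeding arm", on a difference of 5 points and "an estimated standard deviation in each feeding group of 15".

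**The concern.** Siblings share parents, home, antenatal care and the mother's milk supply. Several characteristics that the article calls prognostic or records at baseline (antenatal steroids, parental education, socioeconomic status) are common to them. Some correlation between their Bayley scores is to be expected.

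A multiple-birth covariate shifts the expected score for multiples as a group. It does not tell the model that two particular infants belong together, so co-twins still count as two independent observations. A centre effect does not supply this either: it captures what all infants at a centre share, not what two infants of one mother share beyond that.

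What is at stake is the standard error of the primary comparison. If siblings are in the same arm, it is understated and the p-value is too small. If they are in opposite arms, it is overstated and information is wasted.

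**Working it through.** **Inputs from the article:** difference 5, SD 15, power 80%, alpha 0.05, two successive losses of 10%, 142 evaluable and 176 randomized per arm, 363 in total, four centres. Sidedness is not stated; two-sided reproduces the figure.

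**Assumed, because the article does not give them:** f, the share of analysed infants whose co-twin is also analysed, 0.10 to 0.30; ρ, the correlation between co-twins' scores, 0.3 to 0.7. The product fρ then runs from 0.03 to 0.21.

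**1. The plan's own figures.** n = 2 × (1.960 + 0.842)² × 15² / 5² = 2 × 7.849 × 9 = 141.3, so 142 per arm. Then 142 / (0.9 × 0.9) = 175.3, so 176 per arm; 2 × 176 + 11 = 363. All reproduce, with no allowance for siblings.

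**2. Design effect.** If a share c of twin pairs has both members in the same arm, the variance of the treatment difference is multiplied by DE = 1 + fρ(2c − 1). This gives 1 + fρ when all pairs share an arm (c = 1), 1 − fρ when all are split (c = 0), and 1 when half do each (c = ½).

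**3. Consequences.**
- Model SE / true SE = 1/√DE.
- Type I error of the centre-only test = 2[1 − Φ(1.96/√DE)].
- Power of a valid test at 142 per arm = Φ(5 / (1.780 × √DE) − 1.96), where 1.780 = 15 × √(2/142).

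| Siblings | fρ | DE | Model SE / true SE | Type I error | Valid power |
|---|---|---|---|---|---|
| Same arm | 0.03 | 1.03 | 0.985 | 0.054 | 79.0% |
| Same arm | 0.21 | 1.21 | 0.909 | 0.075 | 72.4% |
| Independent | any | about 1 | 1.00 | 0.050 | 80.2% |
| Split | 0.03 | 0.97 | 1.015 | 0.047 | 81.4% |
| Split | 0.21 | 0.79 | 1.125 | 0.027 | 88.5% |

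**4. Simulation check** (284 infants, four centres, 6,000 runs per setting, f = 0.30, ρ = 0.5):

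| Siblings | Empirical SE | Centre-only SE | Type I, centre-only | Mother-clustered SE | Type I, mother-clustered |
|---|---|---|---|---|---|
| Same arm | 1.94 | 1.79 | 0.070 | 1.90 | 0.056 |
| Independent | 1.80 | 1.79 | 0.055 | 1.77 | 0.058 |
| Split | 1.62 | 1.78 | 0.033 | 1.64 | 0.052 |

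The simulation standard error of a 5% rate is √(0.05 × 0.95 / 6,000) = 0.003. Mother-clustering brings the same-arm and split cases close to nominal and does not improve the independent case.

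**5. How close blocked allocation comes to c = ½.** If co-twins fall in one stratum and are drawn consecutively, and both block sizes are equally frequent, they are split with probability [3 × 2/3 + 7 × 4/7 + 2 × 1/2] / 12 = 7/12. Then 2c − 1 = −1/6 and DE = 1 − fρ/6, which is 0.995 to 0.965, with type I error 0.049 to 0.046. That is still about 5%, leaning slightly conservative.

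**6. Robust variance clustered on centre.** Siblings at one centre would be nested in the cluster, so in principle this absorbs their correlation. With four clusters, the uncorrected version had type I error of about 0.17 to 0.20 in the same simulations, with or without twins.

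**The case against.** A reader might infer that the primary standard error is wrong whenever two siblings are enrolled. The article does not support that. It describes infants as the randomized unit and stratifies by birth weight, which can put co-twins on different lists. Nowhere does it describe allocating siblings together or apart. Under independent randomization of each infant, the centre-only test has about its nominal error on average, and 142 and 176 stand. The inflated error and the loss of power both need a same-arm rule that the article does not state. This part of the objection stands.

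It is also fair that the magnitude rests on assumed inputs. Recorded multiple birth does not mean that the co-twin was enrolled: the co-twin could weigh 1500 g or more, have died, or lack consent. The simulation omits treatment duration, and the correlation that remains after that term may be lower. The low end of the range allows for this, and the effect there is small.

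Finally, a journal article condenses the full protocol, and a sibling allocation rule may well be in a document not shown. Its absence here is therefore not itself the fault. The objection goes too far, however, if it treats the correlation structure in the same way. The article states that structure explicitly, and an analysis that follows it would leave siblings out. The poor behaviour of a four-cluster robust variance is a separate weakness; it matters here only because it closes off one route by which the stated adjustment might have covered siblings.

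**Conclusion.** The point holds in limited form. The stated primary model covers dependence within centre only, siblings can be enrolled, and the secondary model's covariate does not repair this. The standard error can therefore be wrong, and the article does not allow a reader to tell in which direction.

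On the assumed inputs, it is 1.5% to 9% too small if siblings share an arm and 1.5% to 12.5% too large if they are split. It is about right on average if each infant was randomized independently, which is the reading the text favours. In that case a sibling-aware model mainly buys efficiency and a standard error that matches the split of pairs that actually occurred. The documents do not support a claim that type I error is inflated, or that the sample size was miscalculated. The change is worth making because it is cheap and protects against all three cases.

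**What to change.** - **Primary model.** Add a random intercept for mother, or a variance clustered on mother, and enter centre as a fixed effect. With four centres, do not rely on a robust variance clustered on centre. A clustered variance alone corrects the standard error; the efficiency gain needs the random intercept or a working correlation within mother.
- **Other analyses.** Use the same structure for language, motor and growth outcomes and in the multiple imputation.
- **Reporting.** State how siblings were allocated and how many sibling sets were enrolled, with the number in the same and in different arms.

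**Cost:** one identifier linking siblings and a short change of wording. Intervals may widen or narrow slightly, depending on the realised allocation. Recruitment has ended, so the sample size is unaffected. Any other change to the primary covariates, including treatment duration, is a separate matter.

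### The secondary adjusted regression codes birth weight only as the two randomisation strata; adding the recorded weight in grams would gain a little precision at almost no cost

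*Protocol article*

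**What the plan says.** All places are in the protocol article.

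- **Adjusted model (Statistical analyses).** The covariates begin "Sex, birth weight strata (<1000, 1000–1499 g), use of antenatal steroids, multiple birth" and continue with a morbidity count and the duration of feeding with mother's own milk. The stated reason for including them is that they are prognostic of neurodevelopment.
- **Its role (same section).** It is not the main comparison: "we will perform a secondary analysis which will include a regression model adjusted for the aforementioned characteristics".
- **Main comparison (same section).** This is a generalized linear model "controlling for length of treatment and adjusting for correlation of observations taken at the same centre". Birth weight is not named there.
- **Origin of the cut (Methods/Design).** Randomisation was 1:1 in blocks, "with stratification by centre and birth weight grouping (<1000 g and 1000–1499 g").
- **What is recorded (Methods/Design, Table 3).** The baseline variables taken from medical records include "Birth weight, length and head circumference".

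Neither birth weight in grams nor gestational age is in the listed model. No reason is given for using the grouping instead of the measured value.

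**The concern.** The model is fitted because its covariates predict outcome. With a two-level term, a 500 g and a 999 g infant share one predicted level, while a 999 g and a 1000 g infant differ. The 1000 g boundary was chosen to organise randomisation, and nothing in the article suggests that cognitive score steps there. The Discussion describes serious morbidity, poor growth and later sequelae as inversely related to gestation. That is a statement about gestation and not weight, but it describes a gradient.

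If score varies with weight inside each stratum, that variation stays in the residual. The adjusted standard error is then wider than it need be, and a chance difference in weight between arms within a stratum is not adjusted for. What is at stake is some precision in a secondary estimate. The point concerns how a covariate already in the model is coded; it is not a request for a further covariate.

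**Working it through.** **1. The plan's own figures.** Inputs from Statistical analyses: difference 5, SD 15, power 80%, alpha 0.05 (taken as two-sided).

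n per arm = 2 × (1.960 + 0.842)² × 15² / 5² = 2 × 7.85 × 9 = 141.3, rounded up to 142. Allowing for two successive 10% losses, 142 / (0.9 × 0.9) = 175.3, rounded up to 176. Then 2 × 176 + 11 = 363. All three stated figures reproduce, and none depends on how birth weight is coded.

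**2. Information kept by the cut.** If score is linear in weight, the share of the explained variance that the 1000 g indicator retains is the squared correlation between weight and indicator:

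k = p(1 − p)(m₁ − m₀)² / s²

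Here p is the proportion at or above 1000 g, m₁ and m₀ are the mean weights on each side, and s is the SD of weight. Eligibility fixes the upper limit below 1500 g. The article gives no distribution, so the following are assumed.

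| Assumed birth weight distribution | k | Lost |
|---|---|---|
| Uniform 500–1500 g: 0.25 × 500² / (1000²/12) | 0.75 | 25% |
| Uniform from 400 or 600 g to 1499 g | 0.74 | 26% |
| Triangular, rising to 1499 g | 0.70 | 30% |
| Normal truncated to 400–1499 g, location 950–1050 g, SD 250–300 g | 0.65–0.68 | 32–35% |
| The same, location 1000 g, SD 200 g | 0.65 | 35% |
| Untruncated normal cut at its mean: 2/π | 0.64 | 36% |
| Truncated normal, location 900 g, SD 200 g | 0.60 | 40% |
| Truncated normal, location 1200 g, SD 200–300 g | 0.51–0.65 | 35–49% |

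So the loss is about 25–36% when weights centre near 1000 g, and can be larger when they cluster away from it.

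**3. Effect on the adjusted comparison.** Let R² be the share of score variance that continuous birth weight explains (assumed; not in the article), with no other covariates. Then

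SE with the cut / SE with grams = √[(1 − kR²) / (1 − R²)]

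| R² | k = 0.75 | k = 0.64 | k = 0.60 |
|---|---|---|---|
| 5% | 1.007 | 1.009 | 1.010 |
| 10% | 1.014 | 1.020 | 1.022 |
| 20% | 1.031 | 1.044 | 1.049 |

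That is about 0.7–1%, 1.4–2.2% and 3–5%. The top of each range belongs to a 40% loss; at a 36% loss the figures are 0.9%, 2.0% and 4.4%.

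Power for 5 points at 142 per arm, with grams against the cut (k from 0.60 to 0.75):

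- R² 5%: 82.2% against 81.4–81.7%
- R² 10%: 84.2% against 82.6–83.2%
- R² 20%: 88.1% against 85.0–86.1%

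**4. In score points.** The unadjusted SE is 15 × √(2/142) = 1.78. The 95% half-width grows by 1.96 × 1.78 × [√(1 − kR²) − √(1 − R²)]. This is 0.02 points at the mildest corner (R² 5%, k = 0.75) and 0.15 points at the other (R² 20%, k = 0.60), against a 5-point target.

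**5. Sensitivity to shape.** With a true step at 1000 g the indicator loses nothing. With uniform weights and the smooth curved relations tried (logarithmic, saturating, convex), the indicator kept 54–72% of the effect.

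**The case against.** The strongest case against raising this is that nothing is misstated. The model adjusts for the factor that randomisation was stratified on, in the form used to stratify, which is accepted practice. The regression is secondary. The arms are balanced on the cut by design, and an imbalance within strata is ordinary random error that the standard error already covers. The article also condenses a fuller plan, where the form of a covariate might be refined. All of this stands, except that the article does fix the coding, cut point included, so the point is not about missing detail.

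It is also fair that the calculation treats birth weight as the only covariate. The morbidity count in particular may carry part of the within-stratum signal, so for a given retained share the figures above are upper ones. The count is measured after randomisation and donor milk is hypothesised to reduce morbidity, so it is not a clean stand-in for a baseline weight.

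Three stronger readings are not supported:

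- **That a quarter or more of the prognostic information is known to be discarded.** The article gives no distribution, strength or shape from which to know this, and the loss could be nil.
- **That the treatment effect would be biased or the trial underpowered.** Neither follows. The primary model does not use this term, and the sample size reproduces without it.
- **That the loss can be set against the 11 over-enrolled infants.** Those were added because withdrawals, mainly deaths, exceeded the allowance. They have no bearing on the precision of a secondary model.

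**Conclusion.** The point holds as a small, optional improvement in efficiency. The secondary regression uses a two-level version of a baseline variable that the trial records in full, and the article gives no reason for doing so.

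The likely cost is about 1–2% on the adjusted standard error if birth weight explains 5–10% of score variance, and 3–5% at 20%. This rests on a roughly linear relation, weights centred near 1000 g and no recapture by other covariates. No conclusion of the trial is likely to turn on it. The case for acting is that the gain costs almost nothing.

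**What to change.** In the adjusted regression, keep the birth weight stratum indicator, because randomisation used it, and add birth weight in grams as a continuous term. A linear term costs one degree of freedom; a three-knot restricted cubic spline costs two and avoids assuming a straight line. Choose the form before the 18-month scores are analysed; the article reports that follow-up was still under way.

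The change is one phrase in the analysis text. It needs no new data and leaves the sample size and the primary comparison as they are.
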